# Sponsor, investigator, and administrative information

## Title

A prospective, randomized, double-blind, double-placebo, active-controlled, multicenter, interventional study to compare the gastroprotective and pain-relieving effects of Naxozol and celecoxib in patients with osteoarthritis.

## Institution / principle investigator / subinvestigator / manager

## Institution

This study will be conducted in 10 institutions across Korea (for the institution names refer to: 12. Attachments). The list of institutions will be managed as a separate document to that of the protocol document.

## Name and title of principle investigator, sub-investigator and manager

## Name and title of principle investigator and sub-investigator

The signatures and signature forms of the principal investigators at participating institutions are contained within Appendix 5.

The names and titles of the principal investigators, co-investigators, and sub-investigators at participating institutions will be managed as separate documents (see 12. Attachments).

## Name of pharmacist managing investigational products

The list of names of the pharmacists managing the investigational products at participating institutions will be managed as separate documents (see 12. Attachments).

## 1.4. Data Safety Monitoring Committee

A data safety monitoring committee will not be appointed for this study.

# Background and Rationale

## Name of medicinal product and summary of physicochemical characteristics

Product name: Naxozol tablet

Active ingredients: Naproxen (USP) 500 mg and esomeprazole strontium tetrahydrate 24.60 mg (20 mg as esomeprazole)

Form: rectangular pale-yellow film-coated tablet

Summary: Naxozol tablets contain 500 naproxen and 24.60 mg esomeprazole strontium tetrahydrate. Naxozol is a combination drug coated with fast-release esomezol and containing enteric-coated naproxen. The active ingredients contained within Naxozol tablets are as follows:

#### Naproxen

[figure not shown]

Chemical name: (S)-6-methoxy-α-methyl-2-naphthaleneacetic acid Molecular formula: C14H14O3

Molecular weight: 230.26

**Esomeprazole strontium tetrahydrate**

[figure not shown]
Sr2+ • 4H2O

Chemical name: bis (5-methoxy-2-[(S)-[(4-methoxy-3,5-dimethyl-2-pyridinyl)methyl] sulfinyl]-1H-benzimidazole-1-yl) strontium tetrahydrate

Molecular formula: C34H36N6O6S2Sr. 4H2O

Molecular weight: 848.50

## Summary of preclinical metabolic, pharmacokinetic, and ADME study results

Naproxen is a widely used non-steroidal anti-inflammatory drug (NSAID) with a well-known toxicity profile. No carcinogenicity was seen after long-term naproxen administration in a carcinogenicity study in rats. (1)

Esomeprazole is an enantiomer of omeprazole. Hyperplasia of gastric ECL cells was seen in a carcinogenicity study of omeprazole in rats. In a carcinogenicity study in mice, no difference in tumor incidence due to omeprazole administration was seen, although the results were inconclusive. A mutation study of esomeprazole strontium yielded negative results. (2)

## Mechanism of action

Naxozol consists of naproxen and esomeprazole. Like other NSAIDs, naproxen predominantly inhibits the activity of cyclooxygenase-2 (COX-2), thereby decreasing the synthesis of prostaglandin and thromboxane from arachidonic acid, exhibiting anti-inflammatory, analgesic, and anti-pyretic effects. (3)

Esomeprazole is a proton pump inhibitor belonging to the benzimidazole family. It inhibits H+, K+-ATPase in gastric parietal cells. It is able to maintain high gastric pH for a longer period of time than other proton pump inhibitors (the maintenance time at pH >4 is 12 hours for other proton pump inhibitors, but is 16.8 hours for esomeprazole). (4)

## Clinical pharmacological study

A clinical pharmacological study on single-dose oral administration of the Naxozol tablet under fasted conditions indicated that it has a similar safety and tolerability profile as that of the control drug tablet, Vimovo. (5)

Pharmacokinetic results showed that the geometric mean ratio and 90% confidence interval of Cmax and AUClast were 0.99 (0.94 - 1.06) and 1.00 (0.98 - 1.01) for naproxen, and 0.99 (0.82 - 1.18) and 1.04 (0.91 - 1.18) for esomeprazole, both of which are within the range that allows for acceptance of biological equivalence (0.8 - 1.25), showing similar systemic exposure, and, ultimately, the pharmacokinetic equivalence of naproxen and esomeprazole between experimental and control drugs. (5)

## Summary of study subject characteristics

This study will be conducted on Korean osteoarthritis patients older than 50 years who are in need of NSAID therapy.

Osteoarthritis is an indication for this investigational product. Therefore, osteoarthritis patients were considered an appropriate subject disease group and may well benefit therapeutically from treatment with this investigational product.

Upper gastrointestinal bleeding is known to occur in 15-20% of peptic ulcer disease patients and is reported to be the most common complication of peptic ulcer disease. (6,7,8) In particular, while the incidence rate of intestinal perforation or pyloric obstruction is decreasing, that of gastrointestinal bleeds is increasing, presumably as a result of the increased use of NSAIDs, including aspirin, in elderly patients. (6,8) A fifth of elderly patients on NSAIDs develop bleeding from asymptomatic ulcers, requiring caution during history taking and physical examination. (6,9) NSAID use is also reported to increase the incidence of peptic ulcer perforation. Open perforation and resultant bacterial peritonitis are indications for emergency surgery. (6)

Therefore, combination therapy with NSAIDs and gastrointestinal protective drugs such as PPIs or misoprostol is recommended for patients on NSAIDs who have risk factors for peptic ulcer disease (including a history of peptic ulcers, age > 65 years, high-dose NSAID use, concomitant steroid use, concomitant anticoagulant use, or redundant NSAID use including low-dose aspirin) for prevention of peptic ulcers. (10) In the high risk group for peptic ulcer disease, alternative methods for gastrointestinal protection or combination therapy with a selective COX-2 inhibitor and a gastrointestinal protective agent are recommended, rather than the combination of a non-selective NSAID and a gastrointestinal protective agent (e.g. Naxozol tablet). (10) The inclusion / exclusion criteria therefore excluded high risk osteoarthritis patients as subjects in this study.

## Rationale for administration of the investigational product to the study subjects

Symptoms of dyspepsia associated with NSAID use are very common and are reported to occur in 20-25% of NSAID users. (11,12,13,14) However, 40% of NSAID users with endoscopically confirmed erosive gastritis did not show symptoms of dyspepsia, and 50% of patients with symptoms of dyspepsia have normal gastrointestinal mucosa, indicating that symptoms of dyspepsia do not predict damage to gastrointestinal mucosal lining. (11,13,14,15) When compared to non-selective NSAID use, COX-2 inhibitor use is reported to decrease the symptoms of dyspepsia associated with NSAID use. (11,16,17)

Additionally, symptoms of dyspepsia associated with non-selective NSAID use can be reduced with PPIs. PPIs such as omeprazole or esomeprazole are reported to be more effective in symptomatic improvement of dyspepsia than ranitidine or misoprostol. (13,14,18,19)

Therefore, to adequately consider both treatment-related efficacy and safety, either Naxozol tablets or a COX-2 inhibitor were administered to the osteoarthritis patients participating in this study.

## Summary of the efficacy and safety of the investigational product

A clinical study was conducted on the Naxozol tablet, the investigational product for this study. Safety information, including adverse event incidence, is included in Section 5.3.4.1.

In other clinical trials of naproxen and esomeprazole combination drugs, the combination of the two compounds reduced the incidence of gastrointestinal bleeding, upper gastrointestinal adverse events, and the discontinuation rate due to duodenal ulcers, when compared to naproxen alone. (20)

In addition, the long-term safety of combination therapy with the two drugs was confirmed in a 12-month clinical study. (21)

## Experience with the investigational product

The investigational product in this study, the Naxozol tablet, has been used for the treatment of musculoskeletal diseases including osteoarthritis, the indication in this study, since its approval in August 2013.

## Discussion of the risk-benefit of the administration of the investigational product

This study is a phase 4 clinical study on osteoarthritis patients requiring NSAID administration.

The investigational product, the Naxozol tablet, is a slow-release tablet that contains naproxen, an NSAID, and esomeprazole, a PPI.

The clinical efficacy of NSAIDs in pain control in osteoarthritis patients is well accepted. Naproxen, an NSAID, and esomeprazole, a PPI, are both widely used and are safe drugs for pain improvement in osteoarthritis patients and for treatment of gastrointestinal bleeding or symptoms of dyspepsia associated with NSAID use, respectively.

The American College of Gastroenterology (ACG) guideline also recommends co-administration of PPI with NSAID use in patients with a moderate risk of gastrointestinal bleeding. (10)

Furthermore, in conducting this study, the contraindications for the investigational product have already been reflected in the inclusion / exclusion criteria, ensuring exclusion of high risk groups from the study.

In conclusion, a 12-week administration of Naxozol to osteoarthritis patients would not greatly increase the risk of harm to subjects if preceded by appropriate subject selection and followed-up by monitoring of adverse events. The safety of a 12-week oral administration within the given dose range is expected to be satisfactory with careful monitoring of adverse events and vital signs.

## Discussion on study design

This study is a prospective, randomized, double-blind, double-placebo, active-controlled, two-arm parallel, multicenter study. The duration of treatment and observation per subject is 12 weeks, during and after which the safety and efficacy will be evaluated. This duration is considered adequate to evaluate the safety and efficacy outcomes of Naxozol. Relevant discussion and the rationale for other parts of the study design are included in Section 4.2.

## Conclusion

This study is expected to provide the basis for the efficacy and safety of Naxozol in the treatment and prevention of gastrointestinal dysfunction. This study will be conducted in accordance with protocol, good clinical practice (GCP), and other local legislations and regulations.

# Purpose

The purpose of this study was to evaluate the safety and efficacy of the investigational product, the Naxozol tablet, in osteoarthritis patients over 50 years of age after 12 weeks of oral administration.

**Primary purpose**

- To prove non-inferiority of the gastroprotective effect of a 12-week administration of Naxozol in comparison to that of celecoxib in osteoarthritis patients, as evaluated by the Leeds Dyspepsia Questionnaire (LDQ).

**Secondary purpose**

- To compare the gastroprotective effect, as evaluated by the Gastrointestinal Symptom Rating Scale (GSRS), of 12 weeks of treatment with Naxozol or celecoxib in osteoarthritis patients.
- To compare the incidence rate of gastrointestinal (GI) adverse events as well as the drug discontinuation rate due to gastrointestinal (GI) adverse events during 12 weeks of treatment with Naxozol or celecoxib in osteoarthritis patients.
- To compare the pain improvement effect, as evaluated by the visual analogue scale (VAS), after 12 weeks of treatment with Naxozol or celecoxib in osteoarthritis patients.
- To compare the improvement in quality of life (QoL), as evaluated by EQ-5D, after 12 weeks of treatment with Naxozol or celecoxib in osteoarthritis patients.
- To compare patient compliance during 12 weeks of treatment with Naxozol or celecoxib in osteoarthritis patients.
- To compare overall safety during 12 weeks of treatment with Naxozol or celecoxib in osteoarthritis patients.

# Plan

## General study methodology and plan

This is a prospective, randomized, double-blind, double-placebo, active-controlled, two-arm, parallel, multicenter, phase 4 study. Subjects eligible for this study will be randomized on Day 1 into either the experimental or control groups, to receive either two tablets of Naxozol or 1 capsule of Celebrex per day, respectively, for 12 weeks.

#### Dosage and administration of the investigational product

Refer to Section 5.1.1 for dosage and administration of the investigational product. For drugs contraindicated for co-administration, warnings, and packaging and distribution of the investigational product, refer to Sections 5.3 and 5.4.

#### Primary outcome

The primary outcome of the study is to prove non-inferiority of the gastroprotective effect of a 12-week administration of Naxozol in comparison to that of celecoxib in osteoarthritis patients, as evaluated by the Leeds Dyspepsia Questionnaire (LDQ).

#### Secondary outcome

Secondary outcomes are listed in Section 7.3.2 and Section 7.3.3. Secondary outcomes evaluate protection against gastrointestinal dysfunction, pain improvement, quality of life improvement, compliance, and safety.

#### Subjects

This study is conducted on osteoarthritis patients who have agreed to participate in the study, meet inclusion criteria, and do not meet any of the exclusion criteria. The investigator must carefully review a potential subject’s eligibility at the time of enrolment and fully consider the purpose of this study, as well as the rights and health status of the subject. Individuals unable to sign the consent form voluntarily cannot be included in the study. In particular, vulnerable volunteers must be selected with great care and proven feasibility for participation. Inclusion criteria are listed in Section 4.3.

#### Process and evaluation of the study

The screening and following scheduled visits will be conducted on a minimum 106 volunteers from 10 clinical trial sites (subject to change) after written consent is obtained. Information regarding subject allocation (Section 4.4.2), subject drop-out (Section 4.5), and study termination (Section 4.9) is discussed in each respective section.

Refer to ‘Section 6. Study process and evaluation’ for other study procedures, observation categories, and evaluation categories related to this study.

All observations, including all laboratory tests, will be conducted at each clinical trial site according to the pre-specified schedule. At the end of the study, all subjects must physically visit the study sites.

For subjects who drop out early, tests and evaluations corresponding to Visit 3 must be conducted when possible. Subjects who have dropped out cannot be substituted (refer to Section 4.6). If there are continued adverse events, additional visits may be conducted (refer to Section 6.1).

#### Level and method of blinding

- Double-blind.
- This is a double-blind study. Both investigator and subject will be blinded to study group allocation. Hence, they will be blinded as to whether the subject will receive the experimental drug or the control drug. The blinding method and emergency unblinding will be discussed in Section 5.8 ‘Blinding’ and Section 5.9 ‘Emergency unblinding’.
- A placebo will be supplied for each of the experimental (Naxozol tablet) and control (Celebrex capsule) drugs, with the same formulation and packaging so that both investigator and subject cannot distinguish between the active and placebo drugs. This will ensure that the blinding of both investigator and subject to the administered drug is maintained.

#### Treatment-related design

- Multi-dose, parallel treatment group.
- This is a multi-dose, parallel treatment group study. To be selected as a subject of this study, patients must score greater than 40 mm on the pain VAS. The LDQ score on symptoms of dyspepsia associated with NSAID use is expected to decrease after 12 weeks of administration, and, if a cross-over design was applied, the subject’s baseline may not return to a value appropriate for selection criteria after the first round of treatment and before the second round. In addition, gastrointestinal adverse events associated with NSAID use, a secondary outcome of this study, may not improve during the washout period in a cross-over study. Therefore, a parallel design was deemed more appropriate than a cross-over design.

#### Control group

- Active control.
- This study will use the Celebrex capsule as an active control.

#### Subject allocation

Subject allocation is discussed in Section 4.4.2, and randomization is discussed in Section 7.2. After allocation, each subject is assigned a serial number that is used for their identification throughout the duration of the study. A serial number cannot be reused during the study. Stratification recruitment will not be conducted during the allocation. Subjects will be allocated to one of two groups in total: 53 in the experimental group and 53 in the control group.

#### Expected duration of the study

- The expected duration of the subject enrolment period is approximately 21 months.
- The expected duration of the study is approximately 12 weeks from the study initiation date.
- The planned treatment and evaluation period for each subject consists of one day of screening and washout (day of administration) and 12 weeks of treatment and follow-up.
- Each subject will undergo 1 screening visit, 1 randomization and investigational product distribution visit, and 1 follow-up visit.

The general structure of the study is as follows (Figure 1):

#### Figure 1. General structure of the study

| **V1**  **Screening / Washout**  **(D^-^14 - 1)** | **V2**  **Randomization /**  **Investigational product distribution**  **(D1)** | | **V3**  **(End of study)**  **(D84±7)** |
| --- | --- | --- | --- |
| **Screening/ Washout** | | **Drug administration and follow-up visit (12 weeks)** | |

## Review and discussion of the study design

This is a prospective, randomized, double-blind, double-placebo, active-controlled, two-arm, parallel, multicenter, phase 4 study.

## Review of study design

This is a prospective, randomized, double-blind, double-placebo, active-controlled, two-arm, parallel, multicenter, phase 4 study that aims to evaluate non-inferiority of the gastroprotective effect of a 12-week administration of Naxozol tablets in comparison to that of Celebrex capsules in osteoarthritis patients, as evaluated by the Leeds Dyspepsia Questionnaire (LDQ). To reduce investigator- or subject-induced bias in the evaluation of gastrointestinal symptoms, efficacy, or adverse events, a randomized design was used.

## Review of treatment duration

The total duration of treatment per subject is 12-14 weeks, including a screening period (maximum 14 days) and a treatment and evaluation period (12 weeks). The 12-week treatment period is deemed sufficient to observe the change in the LDQ score, the primary outcome.

In a prospective study that compared the symptomatic improvement of dyspepsia between placebo and itopride in functional dyspepsia patients, a change in the LDQ score was observed after 8 weeks of administration. (22) In another study that evaluated dyspepsia in rheumatoid arthritis or osteoarthritis patients using a severity of dyspepsia assessment (SODA) scale instead of the LDQ, symptoms of dyspepsia were evaluated after 12 weeks of treatment. (23)

In conclusion, the 12-week treatment period planned for this study was deemed sufficient to evaluate the efficacy of experimental drug.

## Dose selection and rationale

**Selected dose:** Either 2 Naxozol tablets per day or 1 control drug capsule per day will be administered orally for 12 weeks in order to observe the change in the LDQ score.

The doses used in this study, 1 tablet twice a day for the experimental drug and 1 capsule once a day for the control drug, are both locally approved dosages for osteoarthritis treatment.

## Review of the control drug selection

This is an active-controlled study that uses the Celebrex capsule as the control drug. Celebrex is a selective COX-2 inhibitor, its use resulting in fewer symptoms of dyspepsia associated with NSAID use than with the use of a non-selective NSAID. (11,16,17)

Therefore, the Celebrex capsule was deemed an appropriate control drug for a study regarding dyspepsia symptoms associated with NSAID use.

## Review of the study group allocation

This is a randomized study. In order to reduce bias from the investigator or subject during the safety and efficacy evaluation, this study was designed as a double-blind, randomized study. The randomized design will minimize the effect of baseline characteristics on the results of the study. (24) There will be no stratification during study group allocation.

## Inclusion of special populations as subjects

This study may include elderly subjects, but will not include children, pregnant or lactating women, or other special population groups. Advanced age is a risk factor for gastrointestinal ulceration and bleeding associated with NSAID use. This study will exclude elderly subjects who have other risk factors (including a history of peptic ulcers with or without complications, NSAID use other than low-dose aspirin, and / or anticoagulant or steroid use) through its inclusion / exclusion criteria and drugs contraindicated for co-administration during this study.

## Subject selection

This study will be conducted on osteoarthritis patients aged 50 years or over with a pain VAS score of 40 mm or more.

## Inclusion criteria

- 1. Subjects of Korean nationality who voluntarily decide to participate in the study and provide written consent after receiving and understanding a detailed description and explanation of the study.
  2. Men and women aged 50 years or older at the time of consent.
  3. Persons who are available for follow-up throughout the study duration and are able to perform due tasks for the study, such as reading and filling out EQ-5D and VAS surveys.
  4. Persons with a confirmed medical history of physically symptomatic osteoarthritis who score 40 mm or greater on the pain VAS performed at V2.
  5. Persons deemed appropriate for the study based on the screening results (NB: subjects can be included at the discretion of the investigator even if laboratory test results are outside the reference ranges).

## Exclusion criteria

1. Persons who are participating in a clinical study or have participated in a clinical study within the last 30 days (participation is based on the date of final investigational product administration).
2. Persons with a history of abuse of alcohol or other drugs within 6 months prior to screening.
3. Persons who drink 21 standard drinks or more per week (generally, 55 mL of soju is equated to 200 mL of beer or 30 mL of spirits).
4. Persons with a history of peptic ulcer disease with complications (bleeding, perforation, penetration, and gastric outlet obstruction) within the last 5 years.
5. Persons with a history of peptic ulcer disease without complications within 6 months prior to screening visit or persons with active peptic ulcer disease.
6. Persons who have been infected with helicobacter but did not undergo eradication therapy.
7. Persons with a known history of gastroesophageal reflux disease.
8. Persons with a confirmed diagnosis or clinical suspicion of the following arthropathies that may affect safety and efficacy evaluation: septic arthritis, inflammatory arthropathy such as rheumatoid arthritis, gout, recurrent pseudopain, Paget’s disease, fracture, ochronosis, acromegaly, hemochromatosis, Wilson’s disease, primary osteomalacia, and Ehlers Danlos Syndrome and other genetic collagen disorders.
9. Persons with surgery planned during the study period.
10. Persons with a history of gastrointestinal cancer.
11. Persons with a GI disorder due to a malfunction in drug absorption.
12. Persons with gastrointestinal bleeding, cerebrovascular bleeding, other bleeding disorders, or severe hematological disorders.
13. Persons with moderate to severe hepatic impairment (Child Pugh Class II or higher).
14. Persons with a history of severe heart failure or coronary artery bypass graft (CABG).
15. Persons with severe renal impairment (CrCl <30 mL / min).
16. Persons with severe hypertension (SBP ≥160 mmHg or DBP ≥100 mmHg) refractory to treatment.
17. Persons with a history of allergy to components of the investigational product.
18. Persons with hypersensitivity or allergy to other NSAIDs or PPIs.
19. Subjects who received contraindicated drug or therapy within a pre-specified period prior to study participation (Section 5.3.2).
20. Patients who are receiving contraindicated co-administration drug (Section 5.3.3).
21. Patients who have a history of surgery on the osteoarthritic joint within the past 1 year.
22. Women who are pregnant or breastfeeding, or women of childbearing age who are not using appropriate contraception (condom, diaphragm, intrauterine contraceptive device, or hormonal contraceptive drug, used from 21 days prior to investigational product administration, at least, or male vasectomy); this clause does not apply to menopausal women.
23. Persons deemed inappropriate for study enrollment by the investigator due to clinically relevant medical or psychiatric conditions.
    1. **Subject allocation/investigational product administration**

Subjects who meet the inclusion / exclusion criteria and have given written consent before study participation will be randomly allocated to each study group to receive the investigational products (refer to Section 7.2).

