## Drugs or therapies contraindicated prior to study participation

Subjects who received the following medications for the periods listed below cannot participate in the study:

1. NSAIDs (LDA [≤325 mg / day low dose aspirin] excluded) within 7 days prior to administration of the investigational product.
2. Gastroprotective agents (including H2 blockers, PPIs, misoprostol, etc.) within 7 days prior to administration of the investigational product.
3. IV or oral corticosteroids (oral corticosteroids corresponding to ≤7.5 mg / day prednisone, topical ointments, eyedrops, and nasal agents are excluded) within 7 days prior to investigational product administration.
4. Intraarticular or intramuscular corticosteroids or hyaluronic acid within 8 weeks prior to administration of the investigational product.
5. Glucosamine and / or chondroitin sulfate within 7 days prior to administration of the investigational product.
6. Lithium within 7 days prior to administration of the investigational product.
7. Antiretrovirals (atazanavir, atazanavir sulfate) within 7 days prior to administration of the investigational product.

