## Drugs or therapies contraindicated during study participation

Drugs other than investigational products, especially one of the drugs listed below, should not be administered during the study period, on principle:

1. NSAIDs (LDA [<325 mg/day low dose aspirin] excluded) other than investigational products.
2. Other gastroprotective drugs (H2 blockers, PPIs, misoprostol, etc.).
3. IV or oral corticosteroids (oral corticosteroids corresponding to ≤7.5 mg / day prednisone, topical ointments, eyedrops, nasal agents excluded).
4. Intraarticular or intramuscular corticosteroids or hyaluronic acid.
5. Glucosamine and / or chondroitin sulfate.
6. Lithium.
7. Antiretrovirals (atazanavir, atazanavir sulfate).

All drugs deemed necessary by the investigator, as per the investigator’s medical opinion, can be given. However, if a drug administered without an investigator’s assessment is deemed to have the capacity to influence the safety and efficacy evaluation of this study, the corresponding subject will be excluded from PP analysis. All drugs administered, and their dosage, route of administration, and reason for administration, must be recorded in a case report form signed by the investigator.

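### Section 4.2.6 says elderly anticoagulant users are excluded, but no eligibility criterion or drug-list item names anticoagulants; its ulcer and steroid wording is also broader than the criteria

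*Protocol*

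**What the plan says.** Section 4.2.6 admits elderly subjects, names advanced age as a risk factor for NSAID-related ulceration and bleeding, and then says that elderly subjects with further risk factors will be excluded. Those factors are "a history of peptic ulcers with or without complications, NSAID use other than low-dose aspirin, and / or anticoagulant or steroid use". The stated means are the eligibility criteria and the drugs contraindicated during the study. No time window, dose or age cut-off is given.

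The operative text is as follows:

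- **Ulcer history (4.3.2).** Exclusion 4 covers complicated ulcer within 5 years. Exclusion 5 covers "Persons with a history of peptic ulcer disease without complications within 6 months prior to screening visit", and also active disease.
- **Bleeding (4.3.2).** Exclusion 12 covers "Persons with gastrointestinal bleeding, cerebrovascular bleeding, other bleeding disorders, or severe hematological disorders".
- **Drugs.** Exclusions 19 and 20 point to 5.3.2 and 5.3.3. Item 1 of each list covers NSAIDs other than low-dose aspirin. Item 3 of each covers IV and oral corticosteroids but exempts "oral corticosteroids corresponding to ≤7.5 mg / day prednisone", along with topical, eye and nasal forms.
- **General clause (5.3.3).** The section opens by discouraging every drug other than the study products, then gives seven items, and then allows the investigator to give any drug judged medically necessary.
- **Discretion.** Inclusion 5 admits "Persons deemed appropriate for the study based on the screening results". Exclusion 23 removes "Persons deemed inappropriate for study enrollment by the investigator due to clinically relevant medical or psychiatric conditions".

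**The concern.** A site screens from 4.3, 5.3.2 and 5.3.3, not from a paragraph of design rationale. If a safety exclusion stands only in the rationale, it depends on whether each investigator at the 10 sites happens to apply it.

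The hazard comes from the protocol's own text. Section 5.3.4.5 describes a raised risk of severe gastrointestinal bleeding when warfarin is combined with an NSAID, with no age limit. Section 5.3.5.4 reports significant, potentially fatal bleeding with prolonged prothrombin time on warfarin plus celecoxib, particularly in older patients. Both arms are therefore concerned.

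Nothing scheduled after enrolment would pick up the interaction early. The next planned visit after Day 1 is at about 12 weeks, and the safety laboratory panel (Table 2) has no coagulation test.

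**Working it through.** There is no figure to reproduce for this point. The check sets the four risk factors in 4.2.6 against the 23 exclusion criteria in 4.3.2 and the two 7-item drug lists.

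| Risk factor in 4.2.6 | Where it is put into practice | Result |
| --- | --- | --- |
| NSAIDs other than low-dose aspirin | Item 1 of 5.3.2 and of 5.3.3 | Covered |
| Peptic ulcer, with or without complications | Exclusion 4 (5 years); exclusion 5 (6 months, or active) | Covered within a window |
| Steroid use | Item 3 of both lists; oral use up to 7.5 mg/day prednisone exempt | Covered above a dose |
| Anticoagulant use | 0 of 23 exclusions, 0 of 7 in 5.3.2, 0 of 7 in 5.3.3 | Not named in any of 23 + 7 + 7 = 37 items |

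So one factor of four is covered as stated, two are covered with limits that 4.2.6 does not mention, and one is named nowhere in the operative text. No criterion is specific to elderly subjects; the only age rule is 50 years or older.

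Take a 72-year-old on warfarin with no ulcer or bleeding history:

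1. Exclusions 4 and 5 do not apply.
2. Exclusion 12 concerns bleeding and bleeding or blood disorders, not anticoagulant treatment.
3. Exclusion 19 leads to 5.3.2, where no item matches.
4. Exclusion 20 leads to 5.3.3, where no item matches. The opening clause discourages warfarin as it does any other drug, but the necessity exception in the same section allows it.
5. Inclusion 5 and exclusion 23 leave the decision to the investigator.

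The other mentions of anticoagulants (the risk-factor list in 2.5 and the precaution and interaction text in 5.3.4 and 5.3.5) describe risk or ask for caution. They exclude nobody.

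The sample size does not depend on any of this. It uses the SD, margin, error rates and drop-out only: 2 × 0.65² × (1.96 + 0.842)² / 0.4² = 41.5, rounded up to 42 per arm, and 42 / 0.8 = 52.5, rounded up to 53. Both match section 7.1.

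**The case against.** **Section 4.2.6 is a summary.** It says that exclusion happens through the criteria and lists, so these may be taken to supply the windows and doses it leaves out. The steroid exemption appears identically in both lists and looks deliberate, and the product precautions allow past ulcer with caution. This largely stands for ulcer history and steroids: the mismatch there is loose drafting that needs reconciling, not proof that the limits are wrong. It does not help for anticoagulants, because the lists contain no item that 4.2.6 could be summarising.

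**The opening clause of 5.3.3 already covers anticoagulants.** The seven items are introduced as particular cases of a general default, and exclusion 20 refers to that section. This stands in part. It would be too strong to say that nothing in the protocol bears on anticoagulants. But long-term anticoagulation is an obvious candidate for the necessity exception, so the clause does not produce the firm exclusion that 4.2.6 states.

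**The label permits it.** Section 5.3.5.4 lists patients on anticoagulants under cautious use, and neither contraindication list (5.3.4.2, 5.3.5.2) names anticoagulants, steroids or past ulcer. This stands. Enrolling such a patient would not breach the contraindications. The fault is an exclusion that is stated and not carried out.

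**Conclusion.** The point holds for anticoagulants. An exclusion stated in 4.2.6 has no named counterpart in any of the 37 operative items and rests on a general clause with an exception and on discretion. The ulcer and steroid limits are a secondary inconsistency. The conclusion assumes only that sites apply the criteria and lists as written. The protocol gives no basis for estimating how many subjects would be affected, so no number is offered.

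Two stronger inferences should not be drawn:

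- **That the risk-benefit case in 2.5 and 2.9 fails as well.** Section 2.9 rests on the contraindications being reflected in the criteria, and those do not name these factors. Section 2.5 says that a high-risk group is excluded but does not define it, and it keeps that group apart from patients with risk factors, for whom an NSAID plus gastroprotection is recommended. Only 4.2.6 is clearly contradicted.
- **That the protocol strips protection from at-risk patients on celecoxib.** Section 5.3.2 does rule out "Gastroprotective agents (including H2 blockers, PPIs, misoprostol, etc.) within 7 days prior to administration of the investigational product", and Visit 1 has contraindicated drugs washed out. That is a separate matter of gastroprotection in the control arm. It needs a past-ulcer patient on a PPI who also passes exclusions 6 and 7, and it is not evidence for the mismatch with 4.2.6.

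**What to change.** 1. Add current anticoagulant use as an exclusion criterion in 4.3.2 and as an item in 5.3.3, with no age limit. The warning in 5.3.4.5 has none, and a cut-off at 65 would leave a 64-year-old on warfarin eligible.
2. State at Visit 1 that an anticoagulant is not to be stopped to make a patient eligible. This line is needed because Visit 1 tells sites to wash out contraindicated drugs, which would now include anticoagulants.
3. Reconcile 4.2.6 with the remaining limits. Either write the 5-year, 6-month (or active) and 7.5 mg/day limits into 4.2.6 or, if the broader exclusion is intended, remove those limits for elderly subjects and define the age. The protocol uses both over 65 (2.5) and 65 or more (5.3.5.4), so one must be chosen.

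Deleting anticoagulants from 4.2.6 would also remove the contradiction, but it would leave the documented bleeding risk in both arms without a rule.

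The cost is small. Medication history is already taken at Visit 1, so no procedure is added. Some anticoagulated patients become ineligible, which may slow recruitment slightly. A subject who starts an anticoagulant during the study would fall under the existing rules in 4.5.1 and 4.5.2. The sample size and the primary analysis stay as they are.
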